## Introduction

According to a recent estimate, about 425 million adults around the world and an estimated 158.8 million adults in the Western Pacific Region are living with diabetes mellitus (DM) [1]. Among the International Diabetes Federation regions, the Western Pacific Region has the highest number of adults living with DM [1, 2]. Moreover, the prevalence of both type 1 and type 2 DM (T2DM) has increased significantly during recent decades [3]. T2DM, being much more common, has been the main driver for the increase in global diabetes prevalence [3]. The results of the National Health and Nutrition Survey in Japan, released in September 2017, reported that there were an estimated 20 million patients with T2DM and prediabetes, of which 10 million patients had T2DM [4].

Hypertension is present in more than 50% of patients with T2DM and contributes significantly to microvascular and macrovascular diseases in T2DM [5]. Moreover, the incidence of cardiovascular disease markedly increases when the two diseases coexist [6]. Thus, intensive treatment of high blood pressure, in addition to hyperglycemia, is important for patients with T2DM.

Epidemiological studies have shown that excessive salt intake is directly related to cardiovascular mortality and to an increase in blood pressure [7]. Many hypertension guidelines recommend salt restriction, based on studies that have demonstrated a decrease in blood pressure with a reduction in salt intake [8, 9]. We have previously reported in a single-arm trial that nutritional instructions on dietary salt restriction by a national registered dietitian provided to patients with T2DM consuming excessive salt may be beneficial in reducing dietary salt intake and home blood pressure [10]. In that study, daily salt intake was significantly reduced by 0.8 g at 2 months and 0.7 g at 6 months after the instruction. Moreover, morning systolic blood pressure was significantly reduced by 2.7 mmHg at 2 months and 5.8 mmHg at 6 months after the instruction. However, dietitians are usually too busy to see patients during their regular clinic visits. Therefore, it would have great clinical significance if this study can demonstrate that shorter and more focused nutritional instructions given to patients by their regular physicians during regular outpatient visits are effective. It might contribute to reducing the financial burden on patients and also the need for patients to have separate consultations with a dietitian.

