### Inclusion criteria

Patients will be considered for inclusion in the study if they meet all of the following inclusion criteria: willing and able to give informed consent for participation in this study; male or female, aged between 20 and 90 years old; diagnosed with T2DM (we will apply the Japan Diabetes Society’s “Committee report on classification and diagnostic criteria of diabetes mellitus” for diagnosing diabetes [11]); and salt intake ≥ 6 g per day in patients with hypertension [12], salt intake ≥ 7 g per day in female patients without hypertension, or salt intake ≥ 8 g per day in male patients without hypertension [13]. Daily salt intake will be measured using a spot morning urine sample.

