### Statistical methods

A mixed model will be used to analyze the factors involved in sodium intake. Factors and changes in factors that may influence sodium intake will be adjusted in multivariate models. Subgroup analyses will be conducted stratified by age (< 65 years or ≥ 65 years), sex (male or female), body mass index (< 22%, or ≥ 22%), and hemoglobin A1c levels (< 7%, or ≥ 7%) to investigate the coherency of educational effect among subgroups. The secondary outcomes will be compared using separate regression models. The differences of values between the two groups with 95% confidence interval and a *p* value < 0.05 will also be presented. We will use an intention-to-treat analysis. JMP version 11.2.0 software (SAS Institute, Cary, NC, USA) will be used as the statistical software package for the analysis. All analyses will be two-sided, and *p* values < 0.05 will be considered statistically significant. Multiple imputations will be applied if there are missing values. In a previous study, it was shown that after patients with T2DM were given instructions on reducing salt intake, their salt intake declined from 10.3 ± 1.6 g to 9.3 ± 1.9 g per day [10]. Therefore, we have based our sample size calculation on the assumption that the intervention group will show a 1-g reduction in their daily salt intake, and that the salt intake in the control group will remain unchanged. With the two-sided significance level set at 5.0% and power set at 80%, the required sample size will be 90 participants in each group. Assuming a 10% dropout rate [17], a total of 200 participants will be required for both groups combined.

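### The planned 1 g between-arm difference is an uncontrolled pre-post fall carried over whole with no change expected in controls, so the stated power is optimistic

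*Protocol article*

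**What the plan says.** Protocol article, Statistical methods: for the active arm, the calculation supposes "the intervention group will show a 1-g reduction in their daily salt intake". For the comparison arm it allows no movement at all: "the salt intake in the control group will remain unchanged". The source is a previous study in which, after instruction, "their salt intake declined from 10.3 ± 1.6 g to 9.3 ± 1.9 g per day". It continues: "With the two-sided significance level set at 5.0% and power set at 80"%, 90 per group are needed, or 200 in total with 10% dropout. No SD is named for the calculation.

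The Introduction describes the same reference: "We have previously reported in a single-arm trial that nutritional instructions on dietary salt restriction", given by a dietitian and "provided to patients with T2DM consuming excessive salt", may be beneficial. It then gives the result as "daily salt intake was significantly reduced by 0.8 g at 2 months and 0.7 g at 6 months after the instruction".

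Under Inclusion criteria, entry requires an estimated intake of at least 6 g (hypertension), 7 g (women without hypertension) or 8 g (men without hypertension). "Daily salt intake will be measured using a spot morning urine sample", and no repeat reading is described. Study design defines the primary outcome as the change from baseline to 24 weeks. The Control group section says that controls are told their current intake at baseline.

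**The concern.** A pre-post fall in a single-arm study adds together the effect of the instruction, regression to the mean after selection on a high reading, and any response to being measured and told the result. A randomised comparison estimates only what differs between the arms. Using the whole 1 g as the between-arm difference therefore requires every other component to be zero, and the article offers no support for that.

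Its own design points the other way. Entry depends on a high value of a measure that varies from day to day, and controls receive feedback on their intake. Both would tend to lower control values at follow-up. At stake is the planned power, and so how a null result at 24 weeks should be read.

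**Working it through.** **Inputs from the article.** Difference 1.0 g; two-sided 5%; 80% power; 90 per group; 10.3 (SD 1.6) to 9.3 (SD 1.9) g; falls of 0.8 g at 2 months and 0.7 g at 6 months from the same reference; cut-offs of 6, 7 and 8 g.

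**Step 1: the stated 90 per group.** Formula: n per group = 2 × SD² × (1.960 + 0.842)² / difference². At 1.0 g:
- SD 1.6 gives 41.
- SD 1.9 gives 57.
- The pooled SD, √((1.6² + 1.9²)/2) = 1.756, gives 49.
- The SD of change, √(1.6² + 1.9² − 2r × 1.6 × 1.9), gives 97, 69 or 50 for r = 0, 0.3 or 0.5.

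None of these gives 90. Solving for the SD that does: 1.0 / (2.802 × √(2/90)) = 2.39 g. This is larger than either printed SD, so the SD actually used is unknown. The last step does reproduce: 180 / 0.9 = 200.

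**Step 2: power at 90 per group if the net difference is below 1 g.** Power = Φ(difference / (SD × √(2/90)) − 1.960).

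| Net difference (g) | SD 2.39 | SD 1.9 | SD 1.756 |
|---|---|---|---|
| 1.0 | 80% | 94% | 97% |
| 0.9 | 71% | 89% | 93% |
| 0.8 | 61% | 81% | 86% |
| 0.7 | 50% | 70% | 76% |
| 0.5 | 29% | 42% | 48% |

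Example: 0.7 g with SD 1.9 gives 0.7 / (1.9 × 0.1491) − 1.960 = 0.51, and Φ(0.51) = 0.695. With the smallest printed SD, 1.6, power at 0.7 g is still 83.5%.

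**Step 3: how large regression to the mean could be.** This needs assumptions. Take readings as normal before selection, truncated at the cut-off, and solve for the unselected mean and SD that give a selected mean of 10.3 and SD of 1.6. The expected fall is (1 − r) × (10.3 − unselected mean), where r is the correlation of two readings in one person, assumed to lie between 0.7 and 0.2.
- Cut-off 6 g: unselected mean 10.28; fall 0.01 to 0.02 g.
- Cut-off 7 g: unselected mean 10.17; fall 0.04 to 0.11 g.
- Cut-off 8 g: unselected mean 9.08; fall 0.37 to 0.98 g.

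The range is too wide to fix a figure. It also assumes that the qualifying reading is the baseline reading.

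**Step 4: evidence needing no assumed correlation.** The primary time point is 24 weeks. The Introduction puts the earlier trial's fall at 6 months at 0.7 g, against the 1.0 g used for planning. The 0.7 g is itself uncontrolled, so it too makes no allowance for a fall in controls.

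**The case against.** The strongest reply is that the trial is randomised. Regression to the mean acts on both arms alike and cancels in the between-group difference that Statistical methods plans to report with its 95% interval. That stands. A reader might infer that the artefact will be counted as treatment effect in the result; the documents do not support this, and no within-arm test is planned.

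Second, the 2.39 g is back-solved, not stated. With SD 1.9 the plan absorbs a control fall of 0.2 g and still has 81% power. That stands too: how much power is lost depends on an SD that the article does not give.

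Third, a reader might put power at 25 to 57%. Those values come from applying the 8 g cut-off to everyone, with an assumed unselected mean of 9.5 g, SD of 2.0 g and reading-to-reading correlations of 0.3 to 0.7, at SD 2.39. The 8 g cut-off covers only men without hypertension. Patients with hypertension enter at 6 g, and the Introduction puts hypertension above 50% in type 2 diabetes.

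Fourth, it is tempting to say that the earlier trial selected its patients in the same way. The article says only that they consumed excessive salt and gives neither cut-offs nor number of readings.

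Fifth, Table 1 has columns at −8 weeks and 0. If baseline is a second sample, regression to the mean in this trial's change scores is reduced. But Primary outcome lists one baseline, and the table's marks may have shifted in extraction. Either way, the expected between-arm difference is unaffected.

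None of these replies supports setting control change to zero.

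**Conclusion.** The concern holds as a planning point. The zero-change assumption for controls is unsupported, and the between-arm difference implied by the earlier trial is below 1 g. On the SD implied by the article's own 90 per group (2.39 g), any control fall takes power below 80%: 71% at a net 0.9 g, 61% at 0.8 g and 50% at 0.7 g. On the printed SD of 1.9 g, power stays at 81% for 0.8 g, then drops to 70% at 0.7 g and 42% at 0.5 g.

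The firmest anchor is the article's own 0.7 g at 6 months. The size of regression to the mean cannot be fixed from the documents; it is likely small at the 6 g cut-off and could be large only at 8 g. The documents therefore do not establish a particular shortfall, nor that the trial is underpowered on every reasonable SD, and nothing here makes the treatment estimate invalid.

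**What to change.** In Statistical methods:
- Replace the unchanged-control assumption with an expected fall in both arms, and state the net between-arm difference being planned for.
- Reconcile the 1.0 g with the 0.8 g and 0.7 g that the Introduction reports from the same reference, and say which time point the planning figure represents.
- Name the SD used, whether it is of the 24-week value or of the change, and any correlation behind it, so that 90 per group can be reproduced.
- Restate power at 90 per group over net differences of about 0.5 to 1.0 g.

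This costs wording and a less favourable stated power. It needs no more patients and no extra samples. Separating the screening reading from the baseline reading would not replace these changes, because it leaves the expected between-arm difference as it is.

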### Patient and public involvement

Patients are not consulted about how to design a medical protocol, research questions, or outcome measures for an intervention relating to health outcomes. Patients are given a description of the study with their consent forms. They are also provided with results at the conclusion of the study. Control participants are offered the opportunity to be given the protocol at the completion of the study, pending positive outcomes.

## Discussion

Observational studies have indicated that most people consume an excess level of salt and that excessive salt intake may contribute to hypertension, which is a risk factor for various diseases, such as stroke, coronary heart disease, and nephropathy [7]. Therefore, salt restriction is essential for the prevention of cardiovascular disease and is recommended in many guidelines. This study is a randomized controlled trial on the effect of providing patients with simplified instructions on how to reduce salt intake from their regular physician during a regular clinic visit, using standard nutritional guidance materials. Demonstrating that shorter and more focused instructions during regular outpatient visits are effective would have great clinical significance. This protocol will contribute to the literature because it describes a practical intervention that has not been tested previously, and it may serve as guidance to other researchers interested in testing similar interventions.

Results will be reported in accordance with the Consolidated Standards of Reporting Trials (CONSORT) guidelines and will be disseminated via peer-reviewed publications and presentations at national and international conferences.

### Trial status

The trial is ongoing. The protocol version number is R000026346. Recruitment began on April 1, 2016. The approximate date when recruitment will be completed is March 31, 2020.

## Data Availability

Not applicable.

## Abbreviations

DM: Diabetes mellitus
RCT: Randomized controlled trial
T2DM: Type 2 DM
UAE: Urinary albumin excretion
